### Study 2: changes in team members’ practice, knowledge, and self-efficacy

A pre-post study with a single group of stroke rehabilitation clinicians will be conducted. All stroke rehabilitation clinicians from the five participating sites will be invited to participate, and consenting staff will be enrolled. Indicators of practice change, knowledge change, and self-efficacy are described in Table 1. Chart audits will be used to assess practice change [26], knowledge tests prepared by CO-OP trainers will be used to assess knowledge, and a self-report survey will evaluate changes in self-efficacy. These will be administered immediately before the CO-OP KT intervention (−T1), immediately following (T1), and at a 1-year follow-up (T12). To develop an in-depth understanding of team processes, practices, attitudes related to adoption, and sustainability of best practices for cognitive rehabilitation, site-specific focus groups will be held with consenting clinicians before the intervention (−T1) and at the 1-year follow-up (T12).

**Table 1 Tab1:** Summary of key CO-OP stroke publications

Authors	Year	Population description	Study design, intervention and control	Main findings

**Table 2 Tab2:** Outcomes, indicators, and timing for all studies

Outcomes	Indicators and description	Timing
Study 1: health system: data obtained from electronic referral system, health record, and NRS		
Access to inpatient rehabilitation	Monthly totals: # of inpatient rehab referrals, # of admissions, # declined; reasons for declined referrals	• −T28 to −T1 • T1 to T15
Inpatient rehab outcomes	Average monthly functional independence measure (FIM™) motor and cognitive scores (admission, discharge, and change)	• −T28 to −T1 • T1 to T15
	Monthly frequency of discharge locations (home, home with services, assisted living facility, or acute care)	
Study 2: health knowledge: data obtained from stroke rehabilitation team members and chart audits		
Rehabilitation team member practice change	Chart audits will be conducted 6 months (+/−1 month) before CO-OP KT implementation as a baseline and to confirm practice gaps previously identified with interviews [4], and repeated at 6 and 12 months (+/−1 month) following the CO-OP KT intervention. The chart audit review criteria will center around documentation of functional goals (e.g., independence with upper body dressing), rather than impairment-reduction goals (e.g., increase arm strength); evidence of patient involvement in the goal-setting process; evidence of teaching of cognitive and problem-solving strategies as an intervention technique; evidence of use of guided discovery as an intervention technique	• −T6 • T6, T12
Stroke rehab professional self-efficacy with knowledge and skills related to CO-OP	CO-OP essential elements self-efficacy tool: participants are asked to rate their ability to perform 25 elements on a 10-point scale, with 1 indicating that they cannot perform the element at all and 10 indicating that their performance is excellent. Face validity evaluated by five members of the International CO-OP Academy	• −T1 • T1 • T12
Team perceptions and experiences with team processes, practices, attitudes related to adoption and sustainability of best practices for cognitive rehabilitation	Semi-structured site-specific focus group with groups of 5–8 team members at a time. Focus groups will be conducted by experienced facilitator [name] who will begin with an open-ended question “What has been your experience with facilitating recovery in patients with cognitive impairment?” Based on responses, [name] will probe to obtain a thorough understanding of perceptions and experiences from a wide range of team members at each site	• −T1 • T12
Study 3: health outcomes: data obtained from consenting individual patients		
Performance on personally-meaningful, self-selected activities	The Canadian occupational performance measure (COPM) is a standardized instrument for eliciting performance issues from the client perspective, and for capturing perceived changes in performance over time [16]. The COPM has demonstrated test-retest reliability of 0.89 in people with stroke [34]. A change of 2 points or more on the COPM is considered clinically significant [16]	• Admission to inpatient rehabilitation • Discharge from inpatient rehabilitation • 1 month post discharge • 3 months post discharge • 6 months post discharge
Self-efficacy to perform daily activities	The self-efficacy gauge (SEG) was designed to measure an individual’s self-efficacy in his or her ability to perform daily occupations that span a range of self-care, productivity, and leisure activities. Participants are asked to rate their confidence in their ability to perform 28 items, each on a 10-point scale, with 1 representing “not confident at all” and 10 representing “completely confident”. The SEG has very high internal consistency (0.94) and test-retest reliability (0.90) [35]	
Health status	The stroke impact scale (SIS) [36] is a 59-item questionnaire about the perceived impact of stroke on function and everyday life. The SIS evaluates eight domains. Each item is scored on a 5-point Likert scale related to the degree of difficulty the person with stroke is experiencing. The SIS is widely used in stroke intervention studies as an outcome measure and the psychometric properties of the instrument are well defined [36–38]	
Cognitive screening tool	The MoCA is a 30-item test of cognitive impairment that includes elements of short-term memory recall; visuospatial capacity; aspects of executive functioning; attention, concentration, and working memory; language; and orientation [29]. The MoCA has excellent internal consistency (0.83) and test-retest reliability (0.92) [29]	

*CO-OP* cognitive orientation to daily occupational performance, *KT* knowledge transfer

### Study 3: patient activity, participation, and self-efficacy outcomes

To answer question 3, a non-randomized study using historical controls will be conducted. We will compare a group of patients treated by stroke teams who have been exposed to the CO-OP KT intervention (intervention) to a group who have not been exposed (historical control). Prior to the implementation of CO-OP KT, control participants will be recruited, and after the CO-OP KT intervention, intervention participants will be recruited. During the 3-month period when the CO-OP KT intervention is being administered to teams and learning is being consolidated, no recruitment will occur. In addition to data elements universally collected for the ITS Study 1, Study 3 participants will undergo assessments to measure activity performance, participation, and self-efficacy.

Data collection points will occur at the individual patient participants’ admission to rehabilitation, discharge from rehabilitation, and at 1, 3, and 6 months following discharge. Follow-up assessments will be administered by telephone, a feasible and cost-effective alternative to face-to-face assessments [27]. Data will be collected by family member proxy if the patient participant is not capable of a telephone interview [28]. Table 1 provides a description of all outcomes, indicators, and timing of administration.

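### Study 3 lets a relative answer any telephone follow-up scale, including the two defined as the patient's own view (SEG and COPM), so change from discharge can include a change of informant

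*Protocol article*

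**What the plan says.** The Study 3 section places assessments at rehabilitation admission, at discharge, and 1, 3 and 6 months after discharge. On the last three it says "Follow-up assessments will be administered by telephone", and then "Data will be collected by family member proxy if the patient participant is not capable of a telephone interview". The rule is triggered by inability to do a telephone interview, and it names no outcome to which it does not apply.

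The Study 3 rows of Table 2 describe the outcomes:

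- **SEG:** it measures "self-efficacy in his or her ability to perform daily occupations"; "Participants are asked to rate their confidence in their ability to perform 28 items, each on a 10-point scale".
- **COPM:** it is for "eliciting performance issues from the client perspective, and for capturing perceived changes in performance over time".
- **Stroke impact scale (SIS):** a "59-item questionnaire about the perceived impact of stroke on function and everyday life".

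The block is headed "Study 3: health outcomes: data obtained from consenting individual patients", and no proxy version of any scale is mentioned. Under Data analysis, differences between and within groups are to be examined by repeated measures ANOVA, with no reference to who answered. Under Recruitment and sample sizes, participants must have a MoCA score below 26, and patients who need a substitute decision maker are excluded.

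**The concern.** A relative can report what the patient does. A relative cannot report how confident the patient feels, or how the patient rates performance on activities the patient chose. The second kind of answer is what the SEG and COPM are defined to capture, and these scales carry the self-efficacy and activity parts of research question 3.

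Two consequences follow if the rule is applied as written. First, some follow-up SEG and COPM scores would measure a relative's opinion and be pooled with scores that measure the patient's own view. Second, on this text proxies enter only at the telephone visits. A patient who answers in person at discharge and through a relative at 3 months therefore contributes a change score that mixes recovery with a change of informant. This second problem needs no imbalance between the groups.

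**Working it through.** **Reading the text.** Three statements have to be set together.

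1. The proxy rule covers the telephone visits, which are three of the five assessments, without exemption by scale.
2. Two of the scales given at those visits are defined by the patient's own perspective.
3. The analysis treats all visits as repeats of one measure and does not mention the informant.

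The first two cannot both hold for a visit answered by a relative. The third carries the difference into the change over time.

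**The plan's own figure.** The protocol gives no number for proxies. The only reproducible Study 3 figure is the sample size, needed here just for the size of a group. With a difference of 9, SD 8 and 80 % power, and assuming two-sided 5 % (not stated):

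n = 2 × (1.960 + 0.842)² × (8/9)² = 12.4, so 13 per group, as stated.

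A 30 % loss from the 17 recruited leaves 17 × 0.70 = 11.9, so about 12. One patient answered by proxy is then 1/13 to 1/12, about 8 %, of a group mean. That calculation uses the FIM, which is not a scale at issue here.

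**Size of the effect.** Let q be the share of follow-up answers given by proxies and b the mean proxy-minus-patient gap in SD units. Neither is in the protocol, so every value below is an assumption.

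*Within-group change*, with patients answering for themselves at discharge: shift = q × b.

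| q | b | shift (SD) |
|---|---|---|
| 0.30 | 0.25 | 0.08 |
| 0.30 | 0.50 | 0.15 |
| 0.30 | 0.80 | 0.24 |

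*Between-group contrast at follow-up:* bias = (q1 − q0) × b, where q0 is the control share and q1 the intervention share. The last column is the two-sided error rate of a nominal 5 % comparison with 13 per group.

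| q0 | q1 | b | bias (SD) | error rate |
|---|---|---|---|---|
| 0.30 | 0.30 | 0.25 to 0.80 | 0 | 5.0 % |
| 0.10 | 0.30 | 0.25 | 0.05 | 5.2 % |
| 0.10 | 0.30 | 0.50 | 0.10 | 5.7 % |
| 0.10 | 0.30 | 0.80 | 0.16 | 6.6 % |
| 0 | 0.30 | 0.80 | 0.24 | 8.8 % |

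With equal shares of 30 % the contrast is unbiased. The SD grows by a factor √(1 + 0.3 × 0.7 × b²), which is 1.007 at b = 0.25 and 1.065 at b = 0.80.

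*In scale units*, assuming shares of 20 % and 5 % and gaps of 1 COPM point or 30 SEG points:

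- COPM: 0.15 × 1 = 0.15 points, or 0.15/2 = 7.5 % of the 2-point change that Table 2 calls clinically significant.
- SEG: 0.15 × 30 = 4.5 points. The total runs from 28 to 280, a range of 252, so this is 4.5/252 = 1.8 % of the range.

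**The case against.** **Few proxies are likely.** Patients who need a substitute decision maker are excluded, and participants need enough English to complete the assessments, so they are expected to answer for themselves at entry. The proxy is a fallback. This stands as a reason to expect a low share. It does not make the share zero: the trigger is ability to be interviewed by telephone, not legal capacity, and everyone enrolled has some cognitive impairment.

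**The groups may not differ.** A reader might infer that the intervention group will have more proxies, since the programme aims to bring more cognitively impaired patients into rehabilitation, and so that the comparison with historical controls is biased. The protocol does not support so firm a statement. The same MoCA and capacity criteria apply in both periods, and no proxy rate is given for either. Unequal shares are possible, no more.

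**The reach is limited.** A reader might also take all of Study 3 to be affected. It is not. On this text admission and discharge are not telephone visits, so the discharge comparison is untouched.

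**The full protocol may restrict proxies by scale.** An article leaves such handling to it, and the proxy sentence cites a source that is not at hand. The absence of a handling rule is therefore not itself the point. What remains is that the published sentence states who may answer and sets no limit by scale. Nor is the Table 2 heading about consenting patients a clear contradiction, since it can be read as data about those patients.

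**Dropping proxy answers has its own bias.** This stands. The missing values would fall among the most impaired and probably not at random, and a mixed model deals with that only under a missing-at-random assumption. It is a reason to show both analyses. Nor would allowing proxies for the SIS alone be a clean solution, because the SIS is itself a perceived-impact scale.

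**Conclusion.** The point holds as a minor one. The proxy rule, as published, admits relatives' answers to two scales defined as the patient's own view, and the planned analysis would count a switch of informant after discharge as change within the patient. This rests on the text alone.

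The size is unknown and may be small. The shifts of 0.08 to 0.24 SD in within-group change, and of 0 to 0.24 SD in the group contrast, depend wholly on assumed proxy shares and gaps. The 0.24 SD in the contrast needs proxies in one group only, at 30 %, and a gap of 0.8 SD. The capacity exclusion points towards the lower values. Bias between groups is conditional on unequal proxy shares, which the protocol does not show.

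**What to change.** - Record at every contact whether the patient or a relative answered.
- State that proxy and patient answers on the SEG and COPM will not be pooled as if they were the same measure.
- Report SEG and COPM from patient answers only, using a mixed model that keeps the patient's other visits, beside the analysis that includes proxy answers. Show the number of proxy answers by group and visit.

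The cost is one field on the form, one further analysis of each of the two scales, and a mixed model in addition to, or in place of, the repeated measures ANOVA. The drawback is missing SEG and COPM follow-up values among the most impaired, which is why both analyses are needed. The trial status is not yet recruiting, so the field can be added before any data are collected. If the informant is not recorded at the time, it may not be recoverable later.

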### Recruitment and sample sizes

Five inpatient stroke rehabilitation units or combined stroke/neurology units in the TSNs have agreed to participate. Based on past experience, we estimate that the five units together will have approximately 80 admissions per month combined to contribute to the aggregate monthly data. For Study 1 (admission to rehabilitation), we will collect data from all patients aged 18 years or more who have completed inpatient rehabilitation with a primary diagnosis of stroke, defined as Rehabilitation Care Group (RCG) 01.1, 01.2, 01.3, 01.4 or 01.9. For Study 3, a subset of those patients will be recruited and the additional criteria of having at least some cognitive impairment will be applied, determined using the Montreal Cognitive Assessment© (MoCA©) [29]. The MoCA© is a 30-item test of cognitive impairment that includes elements of short-term memory recall; visuospatial capacity; aspects of executive functioning; attention, concentration, and working memory; language; and orientation. Patients with scores lower than 26 will be included. Additionally, patients will be required to have sufficient English language skills to complete the study assessments (see Table 1 for descriptions). Exclusion criteria are neurological diagnoses other than stroke, presence of major psychiatric illness or capacity issues requiring the use of a substitute decision maker under the Ontario substitute decision maker act. Based on data from a published acute rehabilitation CO-OP study [14], a sample size of 13 per group will have 80 % power to detect a between-group difference of 9 points on the FIM™, standard deviation of 8. Allowing for 30 % attrition from all sources, we will recruit 17 participants per group, 34 in total. Based on past projects, we expect a consent rate of one participant per site per month. Thus, recruitment is highly feasible, and will likely be completed in 4 months for each group.

For Study 2 (changes in team members practice, knowledge, and self-efficacy), all clinicians will be invited to participate, and those who provide informed consent will be included in the survey and focus groups. The five stroke teams have approximately 50 staff each, or approximately 250 total. Based on past experience, we expect a participation rate of 50 % for the self-efficacy survey and about 30 % for the focus groups. Therefore, we anticipate running 2 focus groups (1 pre-intervention and 1 post-intervention) with 8–10 participants each at each of the 5 sites, for a total of 10 focus groups. Chart audits will be conducted on 80 charts of patients discharged approximately 6 months (±1 month) before CO-OP KT implementation, and at 6 and 12 months (±1 month) after CO-OP KT implementation, 240 charts total, providing 89 % power to determine a 25 % change in the audit criteria outlined in Table 1 [30].

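### Study 3: recruiting 17 per group does not keep the required 13 after the stated 30 % attrition; about 12 remain, a small but real error in a stated figure

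*Protocol article*

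**What the plan says.** The section on recruitment and sample sizes in the protocol article bases Study 3 on FIM: "a sample size of 13 per group will have 80 % power to detect a between-group difference of 9 points on the FIM", with a "standard deviation of 8". The next sentence turns this into a recruitment target: "Allowing for 30 % attrition from all sources, we will recruit 17 participants per group, 34 in total". The article gives no inflation formula, no alpha and no sidedness for this calculation, and nowhere else does it state another attrition rate or target for Study 3.

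On feasibility, the same section says "we expect a consent rate of one participant per site per month" and expects recruitment to take about 4 months per group at five sites. The data analysis section plans repeated measures ANOVA for Study 3.

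**The concern.** An attrition allowance should leave the required number after the losses. Here the required number (13), the loss (30 %) and the target (17) appear in adjacent sentences, and 17 less 30 % is below 13. So the three figures cannot all hold.

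The article states these numbers itself, so this is not a detail left to a fuller document. At stake is how a null result would be read: a reader would credit it with 80 % power after the planned losses, which the stated target does not quite give. The groups are small, so each participant lost has a visible effect on power.

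**Working it through.** **Inputs** (all from the section on recruitment and sample sizes): difference 9, SD 8, power 80 %, 13 per group needed, 30 % attrition, 17 per group recruited. Assumed: two-sided alpha 0.05 and a simple comparison of two group means.

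**1. Reproduce the 13.** Normal approximation: n = 2 × (1.960 + 0.842)² × 8² / 9² = 2 × 7.85 × 0.790 = 12.4, rounded up to 13. This matches the article. One-sided 0.05 would give 10, so two-sided 0.05 is the setting that fits.

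**2. Reproduce the 17.** 13 × 1.30 = 16.9, rounded up to 17. That the target was reached this way is an inference, since no formula is printed. Dividing by the retained share gives another figure: 13 / 0.70 = 18.6, rounded up to 19.

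**3. What 17 leaves.** 17 × 0.70 = 11.9, about 12 per group (34 × 0.70 = 23.8 in total). The loss that 17 can bear while keeping 13 is 1 − 13/17 = 23.5 %.

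**4. What 19 leaves.** 19 × 0.70 = 13.3, so the 13 are kept. The total is 38, which is 4 more than 34.

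**5. Power at the retained number.** Normal approximation: power = Φ(9 / (8 × √(2/n)) − 1.96). For n = 13 this is Φ(2.868 − 1.960) = 81.8 %; for n = 12 it is Φ(2.756 − 1.960) = 78.7 %. The t-test figures use the noncentral t distribution with 2n − 2 degrees of freedom.

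| Retained per group | Normal approximation | t test |
|---|---|---|
| 12 | 78.7 % | 75.0 % |
| 13 | 81.8 % | 78.6 % |
| 14 | 84.5 % | 81.7 % |

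Like for like, the loss due to attrition is 81.8 − 78.7 = 3.1 points (normal) or 78.6 − 75.0 = 3.6 points (t test). The difference detectable with 80 % power moves from 8.79 to 9.15 FIM points (normal) or from 9.16 to 9.57 (t test).

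**6. Recruitment capacity.** 5 sites × 1 participant per month × 4 months = 20 per group.

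**The case against.** The strongest objection is about size. On the normal approximation, which is the scale that reproduces the plan's 13, 12 per group still give 78.7 %, only 1.3 points short of 80 %. This stands, and it is why the point is minor.

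A reader might infer that the attrition allowance costs the full 5 points from 80 % to 75 %, or moves the detectable difference from 9 to 9.6. The figures do not support that. By t test the plan's own 13 gives 78.6 %, so 1.4 of those 5 points come from the choice of method and only 3.6 from attrition.

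A second objection concerns FIM itself. According to the Study 1 section and Table 2, it is collected routinely, with admission and discharge scores, and Study 3 adds its own assessments to those data. Participants lost during the 1-, 3- and 6-month telephone follow-ups could still have a discharge FIM. If all 17 per group did, t-test power would be 88.9 %. So 12 per group is the worst case for a discharge FIM comparison. The inconsistency remains, because the article applies 30 % from all sources to this very calculation and does not split it by stage.

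Third, the 30 % might have been meant as an add-on to 13. The sentence speaks of attrition, which is a share of those recruited. If an add-on was meant, the real allowance is 23.5 % and the sentence still needs correcting.

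Fourth, a one-sided test at 0.05 would give 84.7 % (t test) to 86.7 % (normal) at 12 per group. It would also need only 10 per group, so it is not the setting behind the plan's 13.

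Finally, the planned analysis is repeated measures ANOVA, and no correlation between visits is given. The power figures here therefore describe the two-group comparison used for sizing, not the planned analysis.

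**Conclusion.** The point holds as a minor arithmetic error in a stated figure. With 30 % attrition, 17 per group leave about 12, not 13; the target falls 2 per group (4 in total) short of the 19 per group that would keep 13. This part rests only on the article's own numbers and holds however the 17 was reached.

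The power cost is 3.1 points by normal approximation (81.8 % to 78.7 %) or 3.6 points by t test (78.6 % to 75.0 %). It depends on two assumptions: two-sided alpha 0.05 and a simple comparison of means. For FIM at discharge it is an upper limit on the harm, provided loss does not exceed the stated 30 %.

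The documents do not support reading this as a serious loss of power for Study 3, nor as proof that 13 was multiplied by 1.3. That step is a good match but not documented.

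**What to change.** **Minimum change:** correct the sentence so that the numbers agree. For example: recruiting 17 per group (34 in total) retains 13 per group if attrition is at most 23 %; with 30 % attrition about 12 per group remain, giving about 79 % power (normal approximation) or 75 % (t test) for 9 FIM points with SD 8. State the alpha and sidedness in the same sentence. The cost is one sentence.

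**Optional change:** raise the target to 19 per group, 38 in total. This restores the plan's own 13 after 30 % loss. It takes 4 more participants and fits within the capacity of about 20 per group over the planned 4 months.

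Nineteen does not secure 80 % by t test, since 13 retained give 78.6 %. That standard needs 14 retained, so 14 / 0.70 = 20 per group, which uses the whole expected capacity with no slack. The article gives the trial status as not yet recruiting, so on that status either change can be made before enrolment.
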